## Abstract

**Objective::**

This clinical study is aimed to evaluate the effectiveness of deer antler extract on child growth.

**Methods::**

This clinical trial is designed to be conducted on 100 children aged 3 to 12 years for 12 weeks (Trial registration code: KCT0007386). We will evaluate changes in height, height percentile, standard deviation score of height, weight, body mass index, waist circumference, hip circumference, bone age, predicted adult height estimated by bone age, human growth hormone level, insulin-like growth factor-1 (IGF-1) level, IGF-binding protein-3 (IGFBP-3) level, IGF-1/IGFBP-3 ratio, and estradiol level. Additionally, we also will evaluate the adverse events during the study.

## 1. Introduction

Growth is a typical feature of childhood and refers to a series of processes that result in body weight and height increasing with age. These processes are affected by heredity, chronic diseases, social environment, nutritional supply, and hormones.^[1]^

The United States US Food and Drug Administration has specified that the height of children with idiopathic short stature (ISS) is less than 2.25 standard deviations from the average of children of the same age and sex. Accordingly, if the predicted adult height is less than 160 cm for men and 150 cm for women, growth hormone (GH) treatment is necessary.^[2]^ Therapy with GH typically yields only modest gains in height (approximately 4–6 cm), and the height in adulthood would generally be below average despite therapy.^[3]^

A previous study proposed that the ISS should not be treated with GH (grade 2C) because there are considerable disadvantages regarding the cost and burden of long-term treatment.^[4]^ Further, there are wide inter-individual variations in treatment outcomes, including no increase in adult height for some children. Although the outcomes are not readily predictable, shorter parental height, older age, and shorter stature at the time of GH treatment initiation are correlated with lower efficacy. In addition, GH treatment becomes less effective as the treatment duration increases, and the amount of GH needs to be increased. If the treatment is stopped, the growth rate temporarily decreases further, and the safety from long-term complications has not been confirmed.^[5]^ According to a study conducted in Korea,^[6]^ domestic GH treatment costs about 10-14 million won per year; thus, cost-effectiveness must be considered, in addition to the fact that daily injections can cause psychological damage to children.^[7]^ Therefore, when GH treatment is considered, it is critical for the provider to discuss realistic expectations with the child and the family.

Considering that there is a social trend for achieving height growth following effective treatments,^[8]^ there is an increasing desire for conducting studies for evaluating the effectiveness of different materials and treatment methods for addressing growth problems. In this regard, materials derived from deer antlers are of great interest, as they are widely used for immunity enhancement, growth, and development of children.^[9]^ To date, studies have reported that deer antler extracts have anti-stress and anti-aging properties, as well as significant efficacy in improving various bodily functions such as hepatobiliary, cardiovascular, immune system, endocrine, hematopoietic action, and glucose metabolism..^[10]^ In this regard, there have been several experiments^[11–13]^ on cells or animals, which led to the assumption that the rapid growth caused by treatment with antler extracts will have a positive effect on the growth of children; however, studies evaluating the validity of this assumption on the human body are scarce.

Therefore, we have designed a prospective clinical trial study to investigate the effects of deer antler extracts on children growth. The results will elucidate the effects of KGC deer antler extracts on growth and the adverse events (AEs) possibly associated with the administration of KGC deer antler extracts in children.

## 2. Methods

### 2.1. Ethics approval

The study will be conducted in accordance with the principles of the Declaration of Helsinki, the Ethical Guidelines for Clinical Research, and the Institutional Review Board (IRB) of Kyung Hee University Korean Medicine Hospital (KOMCIRB 2021-08-003-006). The study protocol was registered with Clinical Research Information Service (KCT0007386). All modifications to the protocol will be approved by IRB before its execution (Additional file 1; http://links.lww.com/MD/H884). Korean medical doctors (researchers) will explain the study to the children and their guardians and acquire written informed consent. If adverse events occur during the study, appropriate medical treatment will be provided immediately until the participant recovers. All participants’ data will be documented by a code number, and the documents will be stored in locked file cabinets with controlled access. There is no plan or intention to use the results of this study for the individual recognition of functional raw materials for health functional foods.

### 2.2. Study design

This is a prospective double-group study protocol, which will be conducted on 100 children aged 3 to 12 years. This study is designed to observe the effectiveness and safety of KGC antlers for growth promotion. The study protocol conforms to the Standard Protocol Items: Recommendations for interventional trials.

### 2.3. Participants

One hundred children from the Kyung Hee University Medical Center will be recruited. The study will be advertised using posters and banners announcing the need for volunteer participants. The participants and their guardians will receive research information, such as objectives, procedures, and potential benefits and harms, through standardized dialogue. Informed consent will be obtained from the children and their guardians before the screening process. Participants are allowed to withdraw from the study at any time. The research procedure will be conducted as shown in Figures 1 and 2.

**Figure 1. F1:**
[figure not shown]
Schematic chart of the study process. BA = bone age, BMI = body mass index, FAS = full analysis set, hGH = human growth hormone, IGF-1 = insulin-like growth factor-1, IGFBP-3 = insulin-like growth factor binding protein-3, PAH = predicted adult height, PPS = per protocol set, SAS = safety assessment set, SD = standard deviation.

**Figure 2. F2:**
[figure not shown]
Schedule of enrollment, intervention, and assessments. (a) Height, weight, and waist and hip circumference. (b) Hematologic and Serum Chemistry test, Urine test, Hormone test, Estradiol. * Researchers will record the dining pattern of the day before using the 24-h recall method. Additionally, researchers will withdraw and check the dietary questionnaire handed out during the previous visit. ** If there was an examination within 4 weeks, it can be used.

If it is determined that the number of study participants does not meet the expectations, changes or additions to the recruitment method will be implemented through discussion between the research sponsor, the person in charge, and the practitioner.

### 2.4. Sample size

The expected difference in height change was set to 0.45 cm.^[14]^ Based on this, the difference between groups was tripled and set at 1.35 cm. The standard deviation (σ) was set to 2.0, which is the standard for growth disorders (less than −2.0 standard deviation from the average of children of the same age and sex). Accordingly, the sample size was calculated using a 2-tailed 5% significance level, 80% power, and a 1:1 allocation. Accordingly, the required number of subjects per group is 35 and the total number of enrolled subjects is 100 (50 in each group), allowing for a 30% withdrawal rate.

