#### 2.9..1. Primary outcome measurement.

Height will be measured using a portable stadiometer (Seca 213, Seca GmbH, Hamburg, Germany; measurement range: 20–205 cm) by a trained nurse at the same time of day with the participant barefoot, and the value will be rounded to 2 decimal places. Height and weight will be measured at baseline and at 6 and 12 weeks.

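### The sample size rests on three times the stated expected difference, with no reason given, so the 80% power does not apply to the effect the plan calls expected

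*Protocol article*

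**What the plan says.** The calculation is in section 2.4 (Sample size) of the protocol article. It begins from a value with a literature citation: "The expected difference in height change was set to 0.45 cm". The next sentence replaces it: "Based on this, the difference between groups was tripled and set at 1.35 cm". The SD is then fixed: "The standard deviation (σ) was set to 2.0, which is the standard for growth disorders", and a parenthesis explains that standard as lying more than 2.0 SDs below the mean for age and sex. The remaining inputs are conventional: "the sample size was calculated using a 2-tailed 5% significance level, 80% power, and a 1:1 allocation". The result is 35 children needed in each arm. Enrolment is set above that figure to cover dropout: "the total number of enrolled subjects is 100 (50 in each group), allowing for a 30% withdrawal rate".

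The primary outcome is height over a 12-week study (section 2.9, primary outcome: "Height and weight will be measured at baseline and at 6 and 12 weeks"). Section 2.10 compares the groups with a two-sample t-test, or a rank-sum test if normality fails.

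**The concern.** A sample size is normally built on the effect the investigators expect or on the smallest effect worth detecting. Section 2.4 labels 0.45 cm as expected and then uses a different number. Neither that section nor the rest of the article supports the factor of three with a conversion between time periods, a dose argument or a minimal important difference.

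At stake is what the 80% means. A reader, an ethics committee or a family would take it as the chance of detecting what the product is expected to do. As written, it is the chance of detecting three times that. It is also the only stated basis for the number of children enrolled.

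**Working it through.** **Inputs, all from section 2.4:** expected difference 0.45 cm; difference used 1.35 cm; SD 2.0; two-sided 5%; 80% power; 1:1 allocation; 30% withdrawal.

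**Step 1: reproduce the plan's figure.** The normal-approximation formula per group is n = 2 × SD² × (1.960 + 0.842)² / difference². With 1.35 cm and SD 2.0, n = 2 × 4 × 7.849 / 1.8225 = 34.45, rounded up to 35. Allowing for withdrawal, 35 / 0.70 = 50 per group, 100 in total. The stated numbers are therefore arithmetically correct. The noncentral t distribution gives 36 per group instead of 35, with 79.5% power at 35, a trivial difference.

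**Step 2: same design, plan's expected effect.** Change only the difference, to 0.45 cm, and keep SD 2.0. The noncentrality is 0.45 / (2.0 × √(2/n)).

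- n = 35 per group: 0.45 / 0.478 = 0.94; power 15.3% (noncentral t; 15.4% by normal approximation).
- n = 50 per group: 0.45 / 0.400 = 1.125; power 20.0% (20.2% by normal approximation).

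For 80% power at 0.45 cm and SD 2.0, the formula in step 1 gives 2 × 4 × 7.849 / 0.2025 = 310.1, or 311 per group. Noncentral t gives 312 per group.

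**Step 3: how far this depends on the SD.** The 2.0 is a count of SDs marking a growth-disorder threshold, whereas the formula needs the SD of 12-week height change in cm. The document gives no such SD, so the values below are assumptions. Power at 0.45 cm, noncentral t, two-sided 5%:

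| Assumed SD (cm) | 35 per group | 50 per group |
|---|---|---|
| 0.5 | 96% | 99% |
| 0.67 | 79% | 91% |
| 0.8 | 64% | 80% |
| 1.0 | 46% | 61% |
| 1.5 | 24% | 32% |
| 2.0 (as written) | 15% | 20% |

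By the normal approximation, 80% power at 0.45 cm holds if the SD is no more than about 0.67 cm with 35 per group, or about 0.80 cm with 50. The first limit also follows from the plan's standardised effect: 1.35 / 2.0 = 0.675, and 0.45 / 0.675 = 0.67.

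**Step 4: rough plausibility of 1.35 cm.** Over 12 weeks, 1.35 × 52/12 = 5.85 cm/year of additional growth; 0.45 cm corresponds to 1.95 cm/year. The Discussion (section 3) uses 4 cm/year of total growth as a monitoring threshold. The Introduction (section 1) says "Therapy with GH typically yields only modest gains in height", put at about 4–6 cm, of which 1.35 cm is 23% (1.35/6) to 34% (1.35/4). These comparisons suggest an ambitious target and are not used in the calculation.

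**The case against.** The strongest reply is that the 15% rests on an SD nobody should accept. If 2.0 is not the SD of 12-week change, power computed from it says little about the real trial. At an SD of about 0.67 cm or less, the inflated effect and the inflated SD offset each other, and 35 per group keeps about 80% power for 0.45 cm. This stands: a reader might infer that the trial will miss its expected effect about five times in six, but the document does not establish that. Nor does it establish that the two choices cancel.

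Second, 35 per group assumes the full 30% withdrawal. The full analysis set in section 2.10 takes in children with primary outcome data who took at least one dose, and carries the last observation forward, so the analysed number may approach 50 per group. This also stands, and is why both sample sizes are shown.

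Third, the tripling might convert a figure from a shorter period to 12 weeks, and a journal article condenses a longer protocol where the reason may lie. That is possible, but the text says nothing of a conversion and calls 0.45 cm the expected difference itself. The supportable statement is that the factor is unexplained. It would go too far to say that the sponsor is known to expect 0.45 cm at 12 weeks.

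Fourth, the plausibility comparisons are loose. The 4 cm/year figure is a floor that at least 95% of children exceed, and the growth-hormone gain is given for idiopathic short stature, whereas this trial has no height criterion for entry. A reader might infer that 1.35 cm is impossible; the document does not support that.

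Finally, a sponsor may choose a target larger than the expected effect. It may, but the choice then needs a reason and the power statement must say what it refers to. Section 2.4 does neither.

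**Conclusion.** The point holds in a limited form. The arithmetic of section 2.4 is right for 1.35 cm, but the plan calls 0.45 cm expected and gives no reason for tripling it, so the 80% does not describe power for the plan's own expected effect. On the plan's own SD of 2.0, that power is about 15% with 35 evaluable per group and about 20% with 50.

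Actual power is unknown rather than shown to be low, because no SD of 12-week height change is given. Over assumed SDs of 0.5 to 1.0 cm it runs from 96% down to 46% with 35 per group and from 99% down to 61% with 50. All figures assume a two-sample t-test at two-sided 5% and a true difference of 0.45 cm. The 312 per group in the working measures the gap on the plan's inputs; it is not a case for enrolling more children.

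**What to change.** Rewrite section 2.4. Remove the tripling; base the calculation on 0.45 cm with a justified SD of 12-week height change in cm; keep 100 children; and report the resulting power over a range of SDs, for both 35 and 50 per group. State the period to which the cited 0.45 cm refers.

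If 1.35 cm is kept, give its justification and say plainly that the 80% applies only to an effect three times the expected one. The effect and the SD should be revised together, since changing either alone would give a misleading power figure.

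The cost is a change of wording and the work of finding a defensible SD. No extra enrolment is proposed. The downside is that the stated power may become less favourable.

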### 2.6. Exclusion criteria

Children who have endocrine diseases (juvenile diabetes, hyperlipidemia, and hypertension), diseases causing growth retardation (growth hormone deficiency due to pituitary disease), chromosomal abnormalities, or abnormal appearances will not be included in the study. Additionally, children who have not been born with a normal range of weight (i.e., they were less than 2.6 kg or > 4.4 kg), have received hormone replacement therapy, calcitonin, phosphonate, and growth hormone treatment within 6 months prior to the screening, or have any clinically significant acute or chronic diseases of the cardiovascular, endocrine, immune, respiratory, hepatobiliary, kidney, urological, neuropsychiatric, musculoskeletal, inflammatory, haemato-oncological, or gastrointestinal system, are not considered for participation. In this regard, children who have taken medicines or health functional foods related to children’s height growth or antipsychotics within three months prior to the study, as well as who have participated in another clinical trial within 1 month prior to the screening test, will be excluded from the study. Furthermore, any child who is determined as inappropriate for study due to other reasons, such as abnormalities in clinical laboratory tests, will be excluded from the trial.

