Deer antlers are cut and dried young male antlers of Cervus nippon Temminck (梅花鹿), Cervus elaphus Linne (馬鹿), or Cervus canadensis Erxleben (大鹿) and are the fastest growing part of the animal tissues. Insulin-like growth factor-1 (IGF-1), which promotes bone growth, is produced in growing deer antlers, and IGF-1 is known to play an important role in the metabolism of osteoblasts that grow bones. Deer antler is originally a representative tonifying yang medicine (補陽藥) and has effects such as tonifying kidney yang (補腎阳), replenishing essence and blood (益精血), and strengthening muscle and bone (强筋骨).^[20]^ Kidney yang (腎阳) activates overall physiological function by warming the organs of the human body. Based on the efficacy of antlers, this clinical study is designed to prove the safety and effectiveness of promoting height and growth in children and adolescents.

The primary outcome item, height change, is the most intuitive item for judging a child’s growth. Generally, children older than 2 years whose height velocity is less than 4 cm/year should be monitored carefully for chronic nutritional deficits or other causes of short stature because at least 95% of children grow faster than 4 cm/year.^[21]^ However, since each subject’s current growth status is different, items such as SDS and height percentile are selected as secondary outcome measurements. In addition, since length growth is not the only growth indicator, weight growth-related indicators such as weight, waist circumference, and hip circumference will be also measured. Further, to determine the effect on future growth, bone age and predicted adult height will be used for growth prediction.

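### The sample-size SD of 2.0 is a unitless cut-off for short stature used as the SD in cm of 12-week height change, so the stated 80% power is not tied to the primary outcome

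*Protocol article*

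**What the plan says.** Section 2.4 starts from a cited study: "The expected difference in height change was set to 0.45 cm". It then states that "the difference between groups was tripled and set at 1.35 cm", without giving a reason for the tripling. The standard deviation σ "was set to 2.0, which is the standard for growth disorders". The bracket that follows explains the figure as lying below −2.0 "standard deviation from the average of children of the same age and sex". No unit is attached to σ and no other source is offered. With a two-sided 5% level, 80% power and 1:1 allocation, the section arrives at 35 per group, and at 50 per group (100 in total) after allowing for 30% withdrawal.

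The outcome to which this applies is defined elsewhere. The Discussion (section 3) says "The primary outcome item, height change, is the most intuitive item for judging a child’s growth", and section 2.9.1 says "Height and weight will be measured at baseline and at 6 and 12 weeks". The Discussion also uses the same 2 SD figure as the definition of short stature.

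**The concern.** A two-sample comparison of means needs the between-child SD of the outcome, in the units of the outcome. Here that is the SD, in cm, of height change over 12 weeks. The 2.0 in section 2.4 is something else. It counts how many SDs of attained height a child lies below the mean for age and sex. It has no unit, it concerns height at one time and not change, and it is a threshold and not a measure of spread. The number that belongs in the formula shares only the letters SD with it.

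The cut-off is not an entry condition either. Section 2.5 admits all consenting children aged 3 to 12, and section 2.6 excludes diseases that retard growth, not short stature as such. This is a side point, because the unit problem would remain even if every child were short.

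At stake is the meaning of the stated power. The plan promises 80% power for 1.35 cm, and a reader cannot tell whether the true figure is higher or lower. Nor can a reader tell whether the trial could detect the 0.45 cm that its own source led the investigators to expect.

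**Working it through.** **Inputs, all from section 2.4:** difference 1.35 cm (3 × 0.45 cm); σ = 2.0; two-sided α = 0.05 (z = 1.960); power 80% (z = 0.842); 1:1 allocation; 30% withdrawal.

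**Step 1. Reproduce the plan's figure.**

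n per group = 2 × (1.960 + 0.842)² × 2.0² / 1.35² = 34.45, rounded up to 35.

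Enrolled per group = 35 / (1 − 0.30) = 50, so 100 in total.

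Power at 35 per group is 80.6% by the normal approximation and 79.5% by the t distribution (the t-based n is 35.4). The stated figures follow from the inputs. Because the difference is in cm, the formula has treated 2.0 as 2.0 cm.

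**Step 2. Look for support for 2.0 cm.** The article gives no SD in cm for height change, over 12 weeks or any other period. The only reason offered for 2.0 is the cut-off.

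**Step 3. See how far the power depends on the missing SD.** The SDs below are assumed. They are not taken from the documents. Power uses the normal approximation with 35 evaluable children per group:

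power ≈ Φ( difference / (SD × √(2/35)) − 1.960 )

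The difference detectable with 80% power is (1.960 + 0.842) × √(2/35) × SD = 2.802 × 0.239 × SD ≈ 0.67 × SD.

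| Assumed SD (cm) | Power for 0.45 cm | Power for 1.35 cm | Detectable difference (cm) |
|---|---|---|---|
| 0.4 | 99.7% | >99.9% | 0.27 |
| 0.6 | 88.1% | >99.9% | 0.40 |
| 0.8 | 65.3% | >99.9% | 0.54 |
| 1.0 | 46.9% | >99.9% | 0.67 |
| 1.5 | 24.0% | 96.4% | 1.00 |
| 2.0 | 15.4% | 80.6% | 1.34 |
| 2.5 | 11.4% | 61.8% | 1.67 |
| 3.0 | 9.1% | 46.9% | 2.01 |

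The SD at which 35 per group gives 80% power for 0.45 cm is 0.45 / 0.67 ≈ 0.67 cm.

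**Step 4. Is 2.0 cm plausible?** The Discussion states that "at least 95% of children grow faster than 4 cm/year". Scaled linearly, 4 cm/year is 4 × 12/52 = 0.92 cm in 12 weeks, so an SD of 2.0 cm would be about 2.2 times that benchmark growth (2.0 / 0.92). Suppose growth is normally distributed and no more than 5% of children fall below 4 cm/year. The mean velocity that an SD of 2.0 cm per 12 weeks would then require depends on the scaling:

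- Each child grows at a constant rate: annual SD = 2.0 × 52/12 = 8.67, so the mean is at least 4 + 1.645 × 8.67 = 18.3 cm/year.
- Growth in separate periods is independent: annual SD = 2.0 × √(52/12) = 4.16, so the mean is at least 4 + 1.645 × 4.16 = 10.8 cm/year.

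Both are far above the benchmark, so 2.0 cm looks too large. The comparison leaves out measurement error, which adds to the SD of measured change, and it rests on normality and on how an annual figure is scaled.

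**The case against.** The strongest reply is that nothing is miscalculated and that the error may be harmless. If the true SD is well below 2.0 cm, as Step 4 suggests, then 2.0 is conservative and power for 1.35 cm exceeds the stated 80%. The sample size also depends only on the ratio 1.35/2.0 = 0.675, so the same 35 per group would give 80% power for 0.45 cm if the SD were about 0.67 cm. The type I error, the endpoint and the analysis in section 2.10 are untouched, and a null result can still be read from its confidence interval and the observed SD.

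All of this stands, and it limits the point. It does not supply the missing basis. A power figure that would be right only by coincidence is still unsupported, and the reassurance for 0.45 cm fails at an SD of 0.8 cm (65%) or 1.0 cm (47%). Condensation into an article does not explain it either, because the article states the derivation and the derivation itself is at fault.

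A reader might go further and say that the protocol contradicts itself, since an SD of 2.0 cm cannot coexist with the 4 cm/year statement. The documents do not support that. The statement concerns annual velocity and true growth. Turning it into a limit on the SD of measured 12-week change takes normality, a scaling rule and an allowance for measurement error, none of which the article gives. It is an argument from plausibility.

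**Conclusion.** The point holds as a fault in an input. Section 2.4 uses a unitless cut-off for attained height as the SD in cm of 12-week height change. The stated 80% power for 1.35 cm is therefore not tied to the variability of the primary outcome.

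The documents do not settle the direction of the error. A reader might infer that the trial is underpowered, or that it can really detect some specific difference much smaller than 1.35 cm. Neither follows, because both need an SD in cm that the article does not contain. Over assumed SDs of 0.4 to 2.0 cm, power at 35 per group runs from 99.7% down to 15% for 0.45 cm, and from above 99.9% down to 81% for 1.35 cm. The 4 cm/year benchmark makes the lower part of that range more believable than 2.0 cm, but does not prove it.

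The correction should be made before results are read against the plan, because the power statement is wrong as written and restating it is cheap.

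**What to change.** In section 2.4:

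1. Delete the sentence that derives σ from the growth-disorder definition.
2. Replace it with an SD, in cm, of 12-week height change in children of this age range, and name its source. The cited study may serve if it reports one, which cannot be seen from the article. Hospital growth records are an alternative.
3. Keep 100 children, and restate power and detectable difference (about 0.67 × SD at 35 per group) over a range of SDs labelled as assumed unless sourced.
4. Show this for both the expected 0.45 cm and the tripled 1.35 cm, and give the reason for the tripling. Correcting the SD alone is not enough: with 1.35 cm kept and an SD of 0.4 to 0.8 cm, the formula asks for only 2 to 6 children per group, which would not explain enrolling 100.

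The cost is a change of wording in section 2.4, with the ethics approval that section 2.1 requires for any modification. No children are added, and no visit or analysis changes. The downside is that the restated power for 0.45 cm may be less favourable than 80%. It falls below that once the SD exceeds about 0.67 cm.
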